### 9.3 Supplementary subgroup analysis

A supplementary subgroup analysis of the intervention has been scheduled to further investigate the difference between the fluid responders and non-fluid responders. Specifically, the difference in intravenous (IV) fluid resuscitation volume (in liters) at three hours will be examined between the fluid responders and non-fluid responders in the intervention group.

### 9.4 Missing data

Subjects participating in this study will be monitored for a relatively brief duration, and it is anticipated that missing data will occur at a minimal rate. Measures will be implemented to mitigate the occurrence of missing data. These measures encompass comprehensive training

and consistent monitoring protocols, among other strategies, aimed at minimizing the likelihood of missing data.

### **9.5 Other study parameters**

Not applicable.

### **9.6 Interim analysis**

Not applicable.

Copy

## 10. ETHICAL CONSIDERATIONS

### 10.1 Regulation statement

The study will be conducted according to the principles of the Declaration of Helsinki (version, date, see for the most recent version: [www.wma.net](http://www.wma.net)) and in accordance with the Medical Research Involving Human Subjects Act (WMO) and other guidelines, regulations and Acts.

### 10.2 Recruitment and consent

Eligible patients are recruited upon arrival at the Emergency Department (ED). To ensure timely intervention in this acute setting, a deferred consent (DC) strategy is employed, facilitated by a proxy if necessary. For DC rationale, see "Rationale for Deferred Consent (DC) Procedure" below.

#### 11.2.1. Recruitment and consent method

1. Upon ED admission, one of the researchers identifies potential study participants meeting the inclusion criteria by information provided by the treating physician. If possible, the patient and/or his/her designated proxy is informed about the study by the researcher, and their consent is sought. If a patient and/or his/her designated proxy does not orally refuse to participate, the patient will be recruited for the study.
2. Once recruited, the patient is randomized according to the study protocol and informed about the randomization results. Following randomization, treatment is promptly initiated as per protocol.
3. The patient themselves and/or his/her designated proxy will be asked to provide deferred consent (DC) within 30 days of the study start. Information about the study will be provided as soon as possible after study entry, which may be at the ED, ICU, or general ward in hospital. If the subject regains mental competence and is capable, their deferred consent for the continuation of their participation in the study must be obtained without undue delay. In cases where the patient is discharged from the hospital and no consent have been obtained, they may be contacted up to three times, and a letter is mailed to obtain deferred consent. Data collection is carried out for a maximum of 30 days from the time of ED arrival. All contact moments will be registered in REDcap' screening field of 'deferred consent'.
4. If the subject does not provide deferred consent, they must be actively informed of the deletion of data previously collected in the study. Throughout the study, participants who signed deferred consent retain the right to withdraw at any time. However, by signing deferred consent, they grant permission to use their collected data for research purposes up to the point of withdrawal.
5. In accordance with the CCMO guidelines on 'deferred consent' in emergency research situations, if a patient passes away before deferred consent is obtained within the 30-day limit, consent for data use is assumed and not sought from legal representatives due to the following reasons:
  - a. Relatives do not have an independent right to review or assess therapeutic or research data as they are no longer legal representatives.
  - b. The patient's wishes cannot be formally established post-mortem, and relatives no longer have a formal role as representatives in the research context.
  - c. The research under 'deferred consent' has been approved by an ethics committee, prioritizing patient benefits over risks.
  - d. Using data from deceased participants can enhance the reliability of research outcomes, benefiting society and future patients.
  - e. Ethical considerations and transparency require informing relatives about data usage, but their objections may not necessarily lead to data exclusion, depending on the circumstances.

- f. If, however, the deceased patient objects against research through a registration in the UMCG Objection Registry, than further data collected will be halted immediately and data that is collected thus far will be destroyed.
6. The CCMO guideline emphasizes that, from a transparency and ethical standpoint, it is reasonable to inform the patients' family about their study participation in the event of their passing. This communication is important for both providing closure for the family and the completion of the study. Families will be notified through a letter that includes a brief summary of the study and their family member's participation. Contact information is included in the letter.

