### 4.3 Exclusion criteria

A potential subject who meets any of the following criteria will be excluded from participation in this study:

- Primary diagnosis of: acute cerebral vascular event, acute coronary syndrome, acute pulmonary edema, status asthmaticus, major cardiac arrhythmia, drug overdose, or injury from burn or trauma, diabetic ketoacidosis, hyper-osmolality syndrome, pancreatitis
- Known aortic insufficiency, aortic abnormalities, or intraventricular heart defect, such as ventral septal defect or atrial septal defect
- Known advanced heart failure – meaning NYHA IV functional class HF, on waiting list for heart transplant, LVAD recipient or chronic inotrope use.
- Known end-stage kidney disease (dialysis-dependent CKD stage 5 or  $\text{eGFR} < 15 \text{ mL/min/1.73 m}^2$ )
- Decompensated liver cirrhosis at ED admission (e.g., ascites, hepatic encephalopathy, or variceal bleeding)

- Hemodynamic instability due to active bleeding
- Patient has received >1 liter of IV fluid prior to study randomization
- Requires immediate surgery
- Transfer from another hospital after initiation of therapy (a.o. referred by another hospital ICU) or another in-hospital setting
- Pregnant women
- Trauma patients
- Suspected intra-abdominal hypertension, based on the presence of portal hypertension (i.e. presence of ascites due to liver cirrhosis, esophageal varices or as measured by Doppler ultrasound)
- Inability to obtain IV access
- Patient uncouples from treatment algorithm
- Patient should be excluded based on the opinion of the Clinician/Investigator
- Not able to commence treatment protocol within 1 hour after randomization
- Potential ICU-admission unwanted by advanced care directive (e.g., limited life expectancy)

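### The protocol names the UMCG Objection Registry only for patients who die before deferred consent, so a registered objector can be randomised, kept if they survive and sign, and deleted if they die first

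*Protocol*

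**What the plan says.** Section 11.2.1 describes enrolment under deferred consent.

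- **Before randomisation (items 1 and 2).** The only stated objection that stops recruitment is an oral one: a patient who, personally or through a proxy, "does not orally refuse to participate, the patient will be recruited for the study".
- **No deferred consent given (item 4).** "If the subject does not provide deferred consent, they must be actively informed of the deletion of data previously collected in the study". Section 8.6 instead lets the participant choose between retention and destruction.
- **Death before deferred consent (item 5).** The default is retention: "if a patient passes away before deferred consent is obtained within the 30-day limit, consent for data use is assumed".
- **Relatives (items 5a, 5b, 5e).** 5a and 5b say that relatives no longer have a formal role. 5e says that "their objections may not necessarily lead to data exclusion, depending on the circumstances", without criteria or a named decision-maker.
- **Registered objection (item 5f).** "If, however, the deceased patient objects against research through a registration in the UMCG Objection Registry", then "further data collected will be halted immediately and data that is collected thus far will be destroyed".

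The list in section 4.3, introduced by "A potential subject who meets any of the following criteria will be excluded from participation in this study", does not include a registered objection. Sections 4.2, 8.2 and 8.3 do not mention the registry either.

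**The concern.** Item 5f sits inside the branch for patients who died before consent. Two people with the same registration, randomised to the same arm, can therefore be handled differently because of what happened to them afterwards. The one who survives and signs stays in the data; the one who dies before anyone signs is erased. Whether a randomised patient remains in the analysis then depends partly on an outcome. Mortality within 48 hours, in hospital and within 30 days are listed endpoints in section 8.1.2, and cardiovascular death is part of the MACE endpoint.

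Because the data are destroyed, no later sensitivity analysis can bring them back. That is why the matter belongs in the protocol's consent procedure and cannot be left to an analysis plan.

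There is also a consent issue that does not depend on the size of any bias. Section 10.3 allows incapacitated patients to be enrolled. They may be unable to refuse orally, so an existing registration could be the only record of their wishes.

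**Working it through.** **The plan's own figure.** The point rests on no figure stated in the protocol, but the sample size in section 4.4 is needed to judge the effect on the primary endpoint. Inputs: 0.65 L (SD 2.85) against 2.02 L (SD 3.44), 85 per group, two-sided 0.05, Welch test.

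- Standard error = √((2.85² + 3.44²)/85) = √(19.956/85) = 0.4845 L.
- Difference / standard error = 1.37/0.4845 = 2.83, which gives 80.25% power by the noncentral t distribution. A simulation with 50,000 replicates gave 80.0%.
- 170/0.9 = 188.9, against 188 stated. The figure is reproduced.

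**What happens to each kind of patient, as written.**

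| Patient | Outcome | Data |
|---|---|---|
| Registered objector | Survives and signs | Kept |
| Registered objector | Survives, no deferred consent | Deleted (item 4), or own choice (section 8.6) |
| Registered objector | Dies after patient or proxy has signed | Outside item 5; kept |
| Registered objector | Dies before consent | Destroyed (item 5f) |
| Not registered | Dies before consent | Kept (item 5), subject to 5e |
| Not registered | Survives, no deferred consent | Deleted (item 4), or own choice (section 8.6) |

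The first and fourth rows show the defect: same registration, different fate, decided by death. The second and last rows show that losses are not confined to deaths.

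**Size of the loss.** Patients lost = 188 × mortality × share of deaths before consent × share with an objection that is acted on. The protocol gives 188 (section 4.4) and 10% in-hospital mortality for sepsis (section 1). It does not give the last two terms. I assume that all deaths occur before consent, which makes the result an upper range, and that 1% to 15% carry an objection that is acted on.

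- Deaths: 188 × 0.10 = 18.8, or 9.4 per arm.
- Lost: 18.8 × 0.01 = 0.2, up to 18.8 × 0.15 = 2.8.
- Observed mortality: (18.8 − 0.19)/(188 − 0.19) = 9.9%, down to (18.8 − 2.82)/(188 − 2.82) = 8.6%, against a true 10%.
- One death deleted from one arm: 9/94 = 9.6% becomes 8/93 = 8.6%, about one percentage point.

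As an extreme, the protocol's 40% mortality for septic shock gives 75.2 deaths. A 20% objection share would then remove 15.0 patients and move observed mortality from 40% to 60.2/173.0 = 34.8%. The trial is not restricted to septic shock, so this only bounds the range.

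**Primary endpoint.** On the protocol's own assumptions, power is 84.1% at 94 per group. Losing 2.8 patients leaves about 92.6 per group and power between 83.3% and 83.7%. Losing 15 leaves 80.9%. Both assume that no other patients are lost.

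**The case against.** The strongest reply is that the consent procedure favours keeping deaths. Item 5 retains them by default, while item 4 requires living patients to consent or lose their data. Taken as a whole, the procedure could retain deaths more readily than survivors. This stands: item 5f taken alone lowers observed mortality, but the net direction across all consent losses cannot be read from the text.

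Several stronger readings may tempt a reader and are not supported:

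- *The registry is consulted only after death.* Item 5f states a consequence, not the time of the lookup. An unwritten earlier check may exist. Nor does the protocol say whether a registration covers trial participation or only data use.
- *Patients leave the data because they died.* Death is necessary for item 5f but not sufficient. A registered objection is also needed, and a death after the patient or a proxy has signed falls outside it.
- *The rule biases the comparison between arms.* A registration made before arrival is independent of allocation, so in expectation a similar share of deaths would be lost in each arm if mortality is similar. The one-point shift above is a chance imbalance, not a systematic effect.
- *Relatives' objections are decided by people who know the arm.* Section 8.2 says that the investigator and physician know the allocation, but nobody is named as decision-maker under 5e, and its wording leans towards retention. Bias by arm through this route is conjecture.

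It can also be said that section 9 makes item 5f largely moot, because it restricts the ITT population to subjects who signed deferred consent. Read literally, that removes every patient who died before a signature, registered or not. This is a separate contradiction with the consent assumed in item 5. It does not justify the missing registry check.

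**Conclusion.** The point holds in limited form. As written, the protocol allows a registered objector to be randomised and treated, and then excludes that person irrecoverably on a condition that includes death before consent. This is an outcome-dependent exclusion after randomisation for a small subset, and it can be avoided.

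The likely size is small: 0.2 to 2.8 of 188 patients if mortality is 10%, every death precedes consent and 1% to 15% of deaths are affected. The protocol gives no registry rate, so this range is an assumption, not an estimate. The consequence falls on mortality and other safety outcomes, where events are few. It is negligible for the primary fluid volume. Neither the net direction of bias nor a systematic difference between arms is shown.

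The change is still worth making. It is cheap, it moves the exclusion to before allocation, and it respects a registered objection before treatment under the trial begins.

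**What to change.** 1. Add a registered objection to research in the UMCG Objection Registry to the exclusion criteria in section 4.3.
2. In section 11.2.1 item 1, have the researcher check the registry at screening, before randomisation. Section 8.2 already assigns a REDCap screening ID at that stage, so the lookup has a natural place. If such a check is already made in practice, write it down.
3. Keep item 5f only for lookups that were missed, and report any resulting deletions by arm and vital status.

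The cost is one exclusion line, one lookup per screened patient and the loss of the few candidates with a registration. With the check in place and no lookup missed, the loss through item 5f from registrations made before arrival is zero.

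Two minor points belong in the same amendment. Reconcile item 5e with 5a and 5b, so that it is clear whether a relative's objection can remove data and who decides; which rule to adopt is for the sponsor and the ethics committee. Reconcile item 5, which assumes consent for the deceased, with the ITT definition in section 9, which requires a signature.

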### 11.2.2 Rationale for deferred consent (DC) procedure

Deferred consent (DC) is crucial in an acute setting where immediate treatment initiation is imperative within one hour of arrival at the Emergency Department (ED). In such critical situations, patients often require urgent medical interventions, and any delay in treatment could have serious consequences for their health and well-being. In emergency medical research, obtaining traditional informed consent upfront may not be feasible due to the time-sensitive nature of the conditions and the need for rapid intervention. By applying a deferred consent (DC) strategy, researchers can prioritize the prompt delivery of essential treatments while ensuring that participants' rights and welfare are still protected.

Our study's approach strikes a balance between the urgent medical needs of the patients and the ethical principles of respecting participants' autonomy and welfare in research practices. Moreover, our study constitutes low-risk emergency research with a broad therapeutic window and harboring the potential for patients to benefit from their study inclusion. (21) Article 6, paragraph 4 of the Medical Research Involving Human Subjects Act (WMO) states that, under strict conditions, subjects may participate in medical research in emergency situations without their (or their legal representative's) prior written consent. Accordingly, our study's consent procedure meets the stringent criteria outlined in the deferred consent procedural guide of the Centrale Commissie Mensgebonden Onderzoek (CCMO). (22) With these considerations in place, we can ethically and effectively implement a deferred consent strategy.

### **10.3 Objection by minors or incapacitated subjects**

Minors will not be enrolled in the trial. Incapacitated patients will be enrolled in the trial, including those with severe sepsis or septic shock, as these conditions can cause the patient to have decreased consciousness. Legal representatives will be informed of the patient's participation in the study and will be asked to provide deferred consent either during treatment or afterward. Additionally, patients who recover and regain capacity can provide consent up to 30 days after receiving treatment at the emergency department.

### **10.4 Benefits and risks assessment, group relatedness**

#### **Benefits**

This intervention study provides patients with a distinctive and personalized treatment plan tailored to their individual hemodynamic changes resulting from infection. By utilizing the Starling SV monitor to assess fluid responsiveness, patients receive a precise administration of IV fluids or prompt initiation of vasopressor therapy based on their specific needs. This approach aims to reduce the risk of prolonged hypotension and fluid overload. Furthermore, this opportunity has the potential to develop personalized medicine and improve treatment strategies for sepsis patients in the emergency department. Additionally, considering the diverse and varied presentation of sepsis as a disease, we have the opportunity to map the hemodynamic endotype of each individual sepsis patient by collecting comprehensive hemodynamic parameters from the database of this study.

**Risks**

The risks associated with using the Starling SV monitor are minimal. There is a slight chance of experiencing minor adverse events, such as skin irritation from the adhesive on the chest wall, though this is generally not expected to be severe. Additionally, there is the potential for the device to malfunction or provide inaccurate readings, as with any medical device. Improper use or misinterpretation of the device's readings by healthcare professionals could lead to incorrect treatment decisions or delays. Moreover, relying solely on the monitor's readings without considering other clinical factors and patient assessments may result in suboptimal patient care or adverse events. To mitigate these risks, it is crucial for healthcare providers to receive proper training in using the device, follow established protocols, and regularly evaluate its performance. This ensures the safety and effectiveness of the device in clinical practice.

Furthermore, incorrect guidance from the Starling SV monitor may lead to insufficient fluid administration, causing hypotension, or excessive fluid administration, resulting in fluid overload. To address these concerns, all patients will receive a standard 1.5 L per day of intravenous fluids after the ED visit, with variations based on factors such as cardiovascular comorbidities. Intravenous fluid administration will be limited to a maximum of 60 ml/kg over three hours to prevent hypervolemia. Additionally, fluid resuscitation effects, i.e. fluid status and tolerance, will be assessed using Point-of-Care Ultrasound (PoCUS) at different time points during the three-hour and 48-hour follow-up period.

By combining the use of the Starling SV monitor with these precautions, we aim to achieve a more precise estimate of the fluids needed and reduce the risks associated with both hypovolemia and hypervolemia.

**Discussion**

In this intervention study, the utilization of the Starling SV monitor provides significant benefits for sepsis patients in the emergency department. By tailoring treatment plans to individual hemodynamic changes, patients receive precise fluid administration and timely initiation of vasopressor therapy, reducing the risks of prolonged hypotension and fluid overload. This personalized approach has the potential to optimize sepsis management and improve outcomes. Although there are minimal risks associated with the monitor, such as minimal adverse events and the potential for device malfunction or misinterpretation of readings, proper training, adherence to protocols, threshold determination and regular evaluation of treatment effect can mitigate these risks and ensure patient safety. Overall, the benefits of the Starling SV monitor outweigh its minimal risks, making it a valuable tool in improving patient outcomes.

**10.5 Compensation for injury**

The sponsor/investigator has a liability insurance which is in accordance with article 7 of the WMO.

The sponsor (also) has an insurance which is in accordance with the legal requirements in the Netherlands (Article 7 WMO). This insurance provides cover for damage to research subjects through injury or death caused by the study.

The insurance applies to the damage that becomes apparent during the study or within 4 years after the end of the study.

**10.6 Incentives**

Not applicable.

## **11. ADMINISTRATIVE ASPECTS, MONITORING AND PUBLICATION**

### **11.1 Handling and storage of data and documents**

Data is handled confidentially by treating physicians and research nurses. A subject identification code list is used to link the data to the subject. The key to the code is safeguarded by the investigator(s). The code is a random number and will not contain any data of the patient, like date of birth or initials, which would enable direct identification of the patient from the code. The handling of personal data will comply with the EU General Data Protection Regulation and the Dutch Act on Implementation of the General Data Protection Regulation. (in Dutch: Uitvoeringswet AVG, UAVG). The computerized files are stored in the FLUIDS study' research drive in the UMCG network. The files are encrypted and password protected. De-identified data may be copied to other computers within the UMCG-network for analysis but will remain password protected. Research data will be stored for 15 years starting from the end of the study.

### **11.2 Monitoring and Quality Assurance**

Since the current protocol is a low-risk study, monitoring will take place once per year. Therefore, a monitor plan will be drawn up before the start of the study and a monitor (internal UMCG pool) will be invited to monitor the study.

